**5. Registration**

**5-1. Procedure**

The investigator confirms that the participant meets all eligibility criteria, fills in the necessary items on the registration form, and saves it in a file. The investigator will start treatment after registration is complete.

**5-3. Precautions**

1. Registration after the start of protocol treatment is not allowed in any case.
2. The investigators should contact the registration office if they have any questions.
3. Except in cases where consent is withdrawn, subjects will not be unregistered.
4. If incorrect registration or duplicate registration is found, the registration office is contacted immediately.
5. Intervention is started within 70 days of enrollment.

**6. Procedure**

**6-1. Research flow**

We recruit patients with PD visiting our institute. We explain the purpose and methods of this trial, and request research participation. Participants are registered after written informed consent. After registration, participants are evaluated by cognitive test (MMSE), motor symptom evaluation (UPDRS part 3, Hoehn-Yahr), MRI, and questionnaire evaluations (BIS-11, QUIP-RS-J, HADS, PDQ-8, MAAS, NPI-Q). For cases with wear-off phenomenon, MMSE, UPDRS, and MRI should be performed in “ON” state. MRI can be skipped in difficult cases, such as for patients with claustrophobia.

Group mindfulness meditation sessions are performed once a week under the guidance of a professional clinical psychologist, including approximately 30 minutes of guidance and 15 minutes of mindfulness meditation. Mindfulness meditation includes body scans and controlled breathing. Participants are required to practice meditation daily for 15 minutes on 6 or 7 days per week. The participants are given instruction papers in each group session for daily home-based practice, and fill in an implementation record. Clinical evaluations are performed in week 2 and week 8, and MRI is conducted within 14 days after week 8 evaluation. Daily mindfulness meditation continues until the final MRI. For evaluation items and schedule, refer to “#9, Inspection items and schedule."

Concomitant prohibited drugs.

From the date of registration to the end of study, new additions and changes to antiparkinsonian drugs, antipsychotic drugs, and antidepressants are prohibited.

**6-2. protocol discontinuation, completion criteria**

　If any of the following items apply, the survey (evaluation / observation) of the subject will be discontinued.

1) Doctor's judgment

・ When it is judged that the underlying disease worsens and treatment should be discontinued.

・ When an adverse event occurs and it is judged that treatment should be stopped.

・ In addition, when it is judged that it is not possible to continue as the subject of this research.

2) When the subject withdraws consent.

3) Non-compliance with research protocol.

If it is found that the eligibility criteria are not met (if eligibility criteria were not met after registration, it will not be considered as discontinuation and will be regarded as "ineligible after registration" and the research participation will be terminated).

4) Other.

If the subject dies.

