**10. Statistics**

**10-1. Population**

The analysis target population in this study is defined as follows: if necessary, the principal investigator, the research secretariat, and the principal data management will discuss and make a decision before fixing the data.

Among the registered patients, the cases excluding duplicate and erroneous registrations are defined as "all registered cases". The group excluding "non-qualified cases" from all registered cases is defined as "all qualified cases".

- Effectiveness analysis target population.

All eligible patients who have undergone protocol treatment even once, excluding those who were found not to meet the eligibility criteria for this study after enrollment.

- Safety analysis target population.

Of all enrolled cases, those who received some or all of the protocol treatment.

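### Section 6-2 stops outcome assessment along with meditation, so some patients in the effectiveness population can have no week-8 BIS-11, and the single-arm estimate probably leans towards benefit

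*Protocol*

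**What the plan says.** Section 6-2 governs when a subject's participation ends. Its opening sentence reads "If any of the following items apply, the survey (evaluation / observation) of the subject will be discontinued". The parenthesis makes clear that data collection stops, and not only meditation.

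Item 1 of that list, the doctor's judgement, has three parts:

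- progression of the illness itself: "When it is judged that the underlying disease worsens and treatment should be discontinued"
- harm arising during the study: "When an adverse event occurs and it is judged that treatment should be stopped"
- a general clause for subjects whom the doctor judges unable to continue in the research.

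Item 2 is withdrawal of consent and item 4 is death. Item 3 is headed "Non-compliance with research protocol", but the text beneath it deals only with eligibility criteria found not to be met, and says that such cases are not regarded as discontinuation.

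Section 10-1 defines the effectiveness population as "All eligible patients who have undergone protocol treatment even once", apart from those found ineligible after enrolment. Section 10-3 specifies a 95% confidence interval and a t-test for the BIS-11 change after 8 weeks. Section 3-2 describes a single-centre, single-arm, open-label pilot.

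The only follow-up after stopping that the protocol mentions is for continuing adverse events (section 7-1). Nothing provides for a week-8 questionnaire once a trigger in section 6-2 has applied.

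**The concern.** The population in section 10-1 and the data-collection rule in section 6-2 do not fit together. A patient who attends one session and is then stopped for worsening disease is in the effectiveness population, yet section 6-2 says that the patient is no longer evaluated. The 8-week change can be computed only in those still under evaluation at week 8.

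The loss is unlikely to be random. Two of the secure triggers are worsening disease and adverse events, and section 7 counts a clinically significant exacerbation of pre-existing symptoms as an adverse event. Patients stopped for these reasons can plausibly be expected to have improved least. With no comparator, there is no second arm in which a similar loss might cancel.

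This cannot be left to a statistical analysis plan. Such a plan can say how missing values are handled, but it cannot recover questionnaires that the protocol says not to collect. Section 1-2 also intends the results as preliminary data for phase III, so an inflated effect would carry forward.

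**Working it through.** **Inputs from the protocol (section 10-2).** Expected BIS-11 change -10.0, SD 8.0; smallest clinically significant change -5.0; two-sided significance level 10%; power 80%; 18 patients required, raised to 20 for ineligible cases. No dropout or discontinuation rate is given.

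**Step 1: reproduce the stated sample size.** The difference to detect is 10.0 - 5.0 = 5.0, so the standardised difference is 5.0/8.0 = 0.625. A one-sample t-test with the exact noncentral t distribution at two-sided 10% gives power of 79.4% at n = 17 and 81.6% at n = 18. The stated 18 reproduces.

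**Step 2: the bias formula.** Let q be the share of treated eligible patients whose evaluation is stopped before week 8.

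- Mean in all treated = (1 - q) × stayers' mean + q × stopped patients' mean.
- Observed mean = stayers' mean.
- Bias = observed mean - mean in all treated = q × (stayers' mean - stopped patients' mean).

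**Step 3: numbers.** Stayers are set at the protocol's -10. The values of q and the stopped patients' change are assumptions.

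| q | Of 20 patients | All-treated mean, stopped change 0 | Overstatement | All-treated mean, stopped worsen by 3 | Overstatement |
| --- | --- | --- | --- | --- | --- |
| 10% | 2 | -9.0 | 1.0 | -8.7 | 1.3 |
| 20% | 4 | -8.0 | 2.0 | -7.4 | 2.6 |
| 30% | 6 | -7.0 | 3.0 | -6.1 | 3.9 |

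Example: q = 20% with stopped patients at 0 gives 0.8 × (-10) + 0.2 × 0 = -8.0, against an observed -10, an overstatement of 2.0.

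If stopped patients change as stayers do, the bias is q × 0 = 0 at every q. If stayers change by only -5 and stopped patients by 0, the overstatement is 0.5, 1.0 and 1.5 points.

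**Step 4: an extreme bound.** Suppose there is no true effect, changes are normal with SD 8, and the patients lost are exactly those with the worst changes. The observed mean is then -8 × φ(c)/(1 - q), where c is the (1 - q) normal quantile. This gives -1.6, -2.8 and -4.0 at q = 10%, 20% and 30%. Real selection would be weaker; this is a ceiling on what selection alone could produce at those shares.

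**Step 5: precision.** At the planned 10% level, power is 85.3% with 20 week-8 values, 81.6% with 18, 77.0% with 16 and 71.6% with 14. Section 10-2 justifies the two patients above 18 by ineligible cases only, so stopped patients have no allowance of their own. This effect is modest compared with the possible bias.

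**The case against.** **Non-compliance.** A reader might infer that too little practice, or a prohibited drug change, ends evaluation, so that the outcome is measured in compliers only. Section 6-1 does say "Participants are required to practice meditation daily for 15 minutes on 6 or 7 days per week", and item 3 of section 6-2 is headed as non-compliance. But the text under that heading covers only unmet eligibility, and no adherence threshold is given. Section 9-1 lists the achievement rate of meditation as an evaluated item, section 9-2 schedules diary evaluation at weeks 2 and 8, and section 10-1 has no adherence exclusion. Adherence is therefore treated as something to measure, and partly adherent patients may well stay in. The documents do not establish the compliers reading. The point rests on item 1, which is explicit.

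**Rarity.** Section 7-2 expects no particular adverse events, and sections 3-5-1, 3-7 and 3-8 describe the intervention as safe and of negligible burden. Treatment stops within 8 weeks may be few, and the 10% to 30% range has no basis in the protocol. This stands, and is why the figures are only illustrations.

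**Crossing -5.** With stayers at -6, stopped patients at 0 and 20% stopped, the all-treated mean is 0.8 × (-6) = -4.8, and a reader might infer that the rule changes the trial's conclusion. That choice of -6 is not the protocol's. At its own -10, 20% stopped gives -8.0 and 30% gives -7.0, neither of which crosses -5. Section 10-3 also does not make -5 a decision rule.

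**Direction and drug changes.** The direction is inferred. Section 2 links improvement of impulse control disorders to lowering dopamine replacement, so a BIS-11 taken after a drug change could fall because of the drug. Including it without distinction could credit meditation with that fall. This stands and is reflected in the fix.

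**Continued registration.** Section 5-3 says "Except in cases where consent is withdrawn, subjects will not be unregistered". That concerns registration and does not restore the assessments ended by section 6-2.

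**Conclusion.** The fault holds for the treatment-stop and doctor's-judgement triggers. Patients stopped under them before week 8 belong to the effectiveness population but by rule have no week-8 BIS-11, so the primary estimate describes those who stayed. For the non-compliance item it is only possible, because heading and text disagree.

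The bias is probably towards benefit, by inference from the nature of the triggers. Its size cannot be derived from the protocol. Under the stated assumptions (stayers -10, stopped patients 0, 10% to 30% stopped) it is 1 to 3 points, against a smallest clinically significant change of 5. It is zero if stopped patients change as stayers do, and as collected the trial would hold no week-8 data to tell these cases apart. Loss through withdrawn consent or death is no part of the fault.

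For a 20-patient exploratory pilot with an unknown, possibly low, rate of stopping, this should be fixed, but it does not by itself invalidate the trial.

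**What to change.** - In section 6-2, separate stopping the intervention from stopping evaluation. Limit the latter to withdrawal of consent, death and ineligibility found after registration. This leaves the clinical decision to stop treatment untouched.
- Collect at least the week-8 BIS-11 on schedule from every other treated eligible patient, by post or telephone if needed, so that the population in section 10-1 can be analysed as defined.
- Record any prohibited drug change with its date, and show the result with and without BIS-11 values obtained after it.
- Reconcile the heading and text of item 3, so that it is clear whether non-compliance is meant to end evaluation or whether the item concerns eligibility only.

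The choice of model for partly observed patients can be left to the statistical analysis plan. The cost is protocol wording, a few extra questionnaires from patients who have stopped meditating, and an estimate that will probably be less favourable.

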**7. Adverse events**

Adverse events are any unfavorable events that occur in the subject within 1 week after the end of the protocol treatment. A clinically significant exacerbation of symptoms that existed prior to this study is also an adverse event. Physiological changes that are considered to have no clinical significance in terms of frequency or degree are not considered as adverse events. If any adverse events are observed in the subject, the investigator should immediately ensure the safety of the subject and provide appropriate treatment, and describe the details in the case report form.

**7-1. Basic matters**

To ensure the safety of subjects, investigators must adhere to the following basics:

1) The investigators must comply with subject inclusion and exclusion criteria.

2) If the subjects are treated by a doctor other than the investigators of this study, they will be notified about participation in this study and its contents.

3) Continuing adverse events at the end of this study will be followed up as far as possible until they disappear or improve.

4) The subject is instructed to contact the investigator immediately if they feel their health is abnormal.

5) If an adverse event that requires treatment occurs, the researcher informs the participant and appropriate medical care is provided.

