**2. Background**

PD is the second most common neurodegenerative disease after Alzheimer's disease, affecting 100~150/100,000 people. PD is caused by degeneration of dopaminergic neurons and presents as motor symptoms, such as akinesia, tremors, and rigidity. No radical cure has yet been developed; the main treatment is dopamine replacement therapy, such as levodopa or dopamine agonists, which is also described in clinical practice guidelines. Conversely, it has been suggested that motor symptoms are only one aspect of PD, and non-motor symptoms have also been highlighted. Psychiatric symptoms, such as depression, apathy, anhedonia, and impulse control disorders (ICDs), are major problems that can reduce quality of life. ICDs have been reported to occur in about 13% of PD patients, and include pathological gambling, binge eating, excessive shopping and hypersexuality. The ICD related symptoms include punding and dopamine dysregulation syndrome. To improve ICDs, dopamine replacement therapy needs to be reduced. Meanwhile, dose reduction of dopamine agonist can induce dopamine agonist withdrawal syndrome (DAWS).

The pathophysiological mechanism of ICDs in PD has not been elucidated. In PD, the dopaminergic neurons in the substantia nigra pars compacta are reduced, but the dopaminergic neuron in the ventral tegmental area, which plays an important role in reward and goal-directed behavior, are relatively preserved. Dopamine replacement therapy has been reported to cause ICDs due to hyperexcitability from the ventral tegmental area to the ventral striatum and frontal lobe. Owing to individual differences in the likelihood of developing ICDs, some vulnerabilities in the reward system have been shown in patients with ICD. In addition, patients with high impulsivity have more severe ICDs. The trait impulsivity itself may therefore be a psychological symptom of PD.

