**3-5. Mindfulness meditation and measurement of outcomes**

3-5-1. Mindfulness meditation and clinical evaluation

The method of mindfulness meditation is as a 15-minute short version^5^, based on conventional mindfulness-based stress reduction (MBSR). Participants take part in a weekly group session (approximately 30 min) of mindfulness meditation for 8 weeks, and are required to practice meditation daily for 15 min on 6 or 7 days per week. Mindfulness meditation includes body scans and controlled breathing. The participants receive instruction papers in each group session for daily home-based practice, and fill in an implementation record. Mindfulness meditation is performed in the resting or lying position, so minimally invasive and safe. In addition to regular meditation, the participants also receive instructions on meditation techniques during daily activities, such as eating meditation and walking meditation. During the period between registration and the final evaluation, the participants are prohibited from changing antiparkinsonian, antipsychotic, or antidepressant drugs. Evaluation comprises the following questionnaire and a medical examination by an investigating doctor.

3-5-2. MRI

MRI will be performed at the Wakayama Minami Radiology Clinic. T1- and T2- weighted, resting-state functional MRI are taken. The imaging time is about 30 minutes. The procedure is the same as for clinical use and the cost is covered by research funding. MRI is performed twice: during the observation period and within 14 days of the final evaluation.

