**11-2. Informed Consent**

Prior to the start of the study, the investigating doctor explains it to the participant in an easy-to-understand manner using the explanation document and consent form. The participant is given sufficient time to think and they confirm they fully understand the contents of the test. The consent form requires date of consent, the signatures of the investigating doctor who gave the explanation and the agreeing participant after receiving the explanation. A copy of the consent form is given to the participants and the original is retained.

The contents of the consent explanation are as follows:

1) This study is a clinical trial.

2) Design and basis of this study (significance, number of registrations, necessity, purpose, etc.).

3) Contents of protocol treatment.

4) Expected effects of protocol treatment.

5) Expected adverse events, sequelae; and their treatments.

About the degree and incidence of expected adverse events, and what to do when they occur.

6) Cost and compensation.

The mindfulness meditation and MRI are funded by this study funds. The likelihood of adverse events is thought to be extremely low. The medical treatment and examinations under this study are covered by insurance, so they will be treated as usual and no special compensation in required if a medical accident occurs, no special compensation is required and it will be treated in typical way. Appropriate use of PD treatment at the time of obtaining consent according to the instructions of the researcher, and treatment for adverse events is performed as ordinary insurance medical treatment.

7) Expected benefits and potential disadvantages.

8) Refusal and withdrawal of consent.

Participants are free to refuse consent prior to participating in the study, and if they have consented, they can freely withdraw their consent, and thus do not suffer any unreasonable medical disadvantages.

9) What to do if an adverse event occurs.

If an adverse event occurs as a result of conducting the study, the investigator will take the best possible treatment.

10) Privacy protection.

Best effort will be made to keep the names and personal information of participants confidential.

11) Ask questions freely.

Provide written contact information for the research office and explain that you can freely ask questions about the study and treatment.

12) Preservation of materials after research.

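### The ban on drug changes has no exception and is not reconciled with the duty to treat adverse events, so the status and collection of the week-8 BIS-11 after a change made for care are undefined

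*Protocol*

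**What the plan says.** **The ban.** Protocol section 6-1: "From the date of registration to the end of study, new additions and changes to antiparkinsonian drugs, antipsychotic drugs, and antidepressants are prohibited". Section 3-5 puts the same ban on the patient from registration to final evaluation: "the participants are prohibited from changing antiparkinsonian, antipsychotic, or antidepressant drugs". The Abstract repeats it under the intervention method and under prohibited drugs. None of these places gives an exception.

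**The care duty.** Section 7-1: "If an adverse event that requires treatment occurs, the researcher informs the participant and appropriate medical care is provided". Section 7 also asks the investigator to secure the patient's safety and treat, and it widens the definition of an event: "A clinically significant exacerbation of symptoms that existed prior to this study is also an adverse event".

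**The link between the two.** Section 2, on ICDs: "To improve ICDs, dopamine replacement therapy needs to be reduced". ICD is not an exclusion criterion in section 4-2, and section 8-2 schedules an ICD scale (QUIP-RS-J) at weeks 0, 2 and 8.

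**The exit rule.** Section 6-2 stops evaluation and observation on a doctor's judgment (worsening disease, an adverse event, or inability to continue), on withdrawal of consent, on non-compliance with the protocol, or on death. It does not mention drug changes. The only text under the non-compliance item concerns eligibility.

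**The analysis.** Section 10-1 defines the effectiveness population as "All eligible patients who have undergone protocol treatment even once", less those later found ineligible. Section 10-3 analyses the 8-week change in BIS-11 with a confidence interval and a t-test.

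**The concern.** When appropriate care for an adverse event means changing a drug in a banned class, sections 6-1 and 7-1 point in different directions and section 6-2 does not decide between them. By the protocol's own account in section 2, improving an ICD is such a case, and impulsivity is the trial's subject.

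The ban can also last a long time. Section 5-3 allows up to 70 days from enrolment to the start of the intervention. Eight weeks of meditation follow, then up to 14 days to the final MRI.

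The primary estimate is at stake in two ways. If evaluation stops after the change, the week-8 BIS-11 is missing for a reason that may be related to impulsivity. If evaluation continues, the value may reflect the drug change as well as meditation. With one arm and a target of 20 patients, no control group offsets either effect.

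**Working it through.** **1. Three readings of a drug change made for care**

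| Reading | Basis | Week-8 BIS-11 | Effectiveness population (10-1) |
|---|---|---|---|
| Permitted care | 7, 7-1 | Collected, may include a drug effect | In |
| Non-compliance | 6-1 with 6-2 item 3 | Evaluation stops, value may be missing | In, if treated once |
| Discontinuation on doctor's judgment | 6-2 item 1 | Evaluation stops, value may be missing | In, if treated once |

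The text does not choose among these rows. In the second and third, section 10-1 counts a patient whose primary outcome section 6-2 may have stopped collecting.

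**2. Length of exposure**

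70 + 56 = 126 days from enrolment to week 8, and 126 + 14 = 140 days to the final MRI, at most.

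**3. The plan's own sample size**

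Inputs from section 10-2: expected change -10.0, SD 8.0, smallest relevant change -5.0, two-sided alpha 10%, power 80%. The difference tested is 10 - 5 = 5.

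- Normal approximation: n = (8 × (1.645 + 0.842) / 5)² = 15.8, so 16.
- Exact one-sample t-test (noncentral t): n = 18, power 81.6%. This reproduces the stated 18.

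**4. If week-8 values are lost**

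Same inputs, exact t-test:

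| Patients analysed | Power |
|---|---|
| 20 | 85.3% |
| 18 | 81.6% |
| 17 | 79.4% |
| 15 | 74.4% |

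Section 10-2 raises 18 to 20 to allow for ineligible cases, not for lost outcomes. Three losses from 20 leave 17. Three losses after two ineligible cases leave 15.

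**5. How far the mean could move (assumption, not an estimate)**

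Let k of n patients be affected, each by d points.

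- If they stay in and the drug change adds d to their BIS-11 change, the mean moves by k × d / n.
- If they drop out and their change would have differed by d from the others, the mean of those remaining differs from the full mean by the same k × d / n.

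The documents give neither k nor d. Assume n = 20, k = 1 to 3 and d = 5 to 15 in size:

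- lowest: 1 × 5 / 20 = 0.25 points, or 0.25 / 5 = 5% of the smallest relevant change;
- highest: 3 × 15 / 20 = 2.25 points, or 2.25 / 5 = 45%.

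The sign is open.

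**The case against.** The strongest reply is that a drug restriction, a duty of care and a discontinuation list form an ordinary structure. Section 7-1 does not order a change in a banned class, and section 6-2 lets the doctor take the patient out. That is right as far as it goes: the sections conflict only when care means changing a banned class. But section 6-2 never links a drug change to the ban, and taking the patient out costs the outcome.

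A second reply is that handling of values after a drug change may sit in an SAP that is not shown, that section 7 already puts adverse-event details on the case report form, that section 16-1 monitors deviations and reasons for discontinuation, and that section 10-1 allows population decisions before data are fixed. This also stands in part: the absence of a handling rule is not itself a finding. However, an SAP cannot recover a value that section 6-2 told the investigator not to collect.

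A reader might infer four stronger things, which the documents do not support:

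- **That a patient is either held on a drug or changed and counted as a meditation responder.** Section 6-2 offers a third route, and the protocol has no responder endpoint. Section 10-3 analyses the change in score.
- **That section 11-2 adds a conflicting care rule.** Its line "treatment for adverse events is performed as ordinary insurance medical treatment" stands under cost and compensation and says how treatment is paid for.
- **That the 13% ICD frequency in section 2 counts those affected.** It gives 20 × 0.13 = 2.6 patients and 1 - 0.87^20 = 94% for at least one, but these are patients with an ICD. A stable ICD present at entry is not an adverse event under section 7, and no rate of worsening or drug change is given.
- **That a drug change must flatter meditation.** No document gives a drug effect on BIS-11, and section 2 also warns that reducing a dopamine agonist can cause a withdrawal syndrome.

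**Conclusion.** The point holds as an inconsistency in the protocol's text. The ban is written without exception, the care duty can require what the ban forbids, and the exit rule leaves the resulting drug change unclassified. Two of the three readings stop evaluation in a patient who remains in the effectiveness population.

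The consequence is a week-8 BIS-11 that may be selectively missing or may be mixed with a drug effect, in a design with no comparator. The documents establish neither how many patients would be affected nor which way the mean would move. The 0.25 to 2.25 points and the power figures show scale only. They rest on assumed counts and assumed point differences, and the power figures also rest on the inputs of section 10-2. The stated sample size of 18 is not in dispute.

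**What to change.** 1. Reconcile sections 3-5, 6-1, 6-2, 7, 7-1 and 10-1, and the matching Abstract rows, so that one rule states how a drug change made for care is classified: permitted, deviation or discontinuation. Which clinical rule applies is for the investigators, and none is proposed here.
2. Record the date, drug class and reason for every change in the listed classes.
3. Amend section 6-2 so that the week-8 BIS-11 is still collected after such a change, or after meditation stops, unless consent is withdrawn. As written, section 6-2 would stop it.
4. Report the 8-week BIS-11 change with and without values obtained after a drug change.

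The cost is protocol wording, one line on the case report form and one supportive estimate. That estimate rests on slightly fewer patients and should be read alongside the main result, because leaving those patients out is itself a selection.
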